#### Interventions

There will be two knowledge transfer interventions with different delivery methods. The learning objectives, content covered, and number of contact hours will be similar for both. The KT will address how to: select health status measures for clinical practice, score/interpret results, incorporate measures into clinical reasoning, and recognize and address personal and organizational barriers and facilitators of change.

#### Stakeholder-Hosted Interactive Problem-based Seminars (SHIPS)

The SHIPS will consist of a 2 1/2-day interactive PBL sessions with 10 hours of contact/tutorial time and 15–20 hours of facilitated independent group work that will focus on application of learned concepts. Consistent with a problem-based philosophy, small groups of clinicians will participate in interactive sessions facilitated by a faculty tutor. The faculty tutor will be a developer of outcome measures, an expert facilitator in PBL, and one of the study investigators. The SHIPS' knowledge transfer strategy is based on evidence establishing the importance of using opinion leaders with scientific and professional credibility [32], and will be operationalized using our experience in PBL as a method of providing contextualized learning. Six "problems" will be generated by faculty through a consultative process with the participants prior to the sessions. Problems will be generated to reflect the established curriculum, with a problem that represents the practice characteristics and issues expressed by participants. Participants will conduct this process four weeks prior to the SHIPS intervention and will receive the curriculum, course objectives, and a recommended reading list one week prior to attendance at the SHIPS.

#### Online Problem-based Course (e-PBL)

The web-based intervention will consist of six weekly e-PBL sessions with 10 contact hours and 10–15 facilitated independent learning activities. Six generic problems will be developed by the study investigators to meet the curriculum objectives. The e-PBL will be delivered over a relatively short period (six weeks) as previous research demonstrated a large drop-out rate with 14 weeks [72]. Sessions will be facilitated and monitored by a faculty member who is familiar with web-based instruction, PBL, and has expertise in outcome measures. Study investigators will ensure visibility through their participation in online chats and content development, but the operation of the online delivery will be managed by an educator with expertise in online delivery. The consistent components of each session will be a problem generated by the faculty to represent key concepts regarding outcome measures, session objectives, a recommended reading list, and discussion questions. Discussion questions will be addressed through asynchronous online chat amongst participants, as facilitated by faculty tutors.

### Study measures

#### Baseline measurement of eligibility, status, and potential KT predictors

Participants will be pre-screened to ensure inclusion criteria. Eligible participants will then complete a baseline knowledge pre-test (to avoid ceiling effects/lack of responsiveness). Participants also will complete a baseline information questionnaire to collect demographic data, practice patterns, and educational background. Survey measures of knowledge and behavior will be administered. This data collection also will include a measurement of the therapist's intent to use outcome measures, their general level of research utilization, and their readiness to change. This scale evaluating Readiness to Change [40,41,73] was developed to reflect the core elements of the five stages of change, but was specifically applied to changing clinical practice. Although all participants will have agreed to allocation during informed consent, they will be asked their preference with respect to e-PBL and SHIPS so that post-hoc analyses can determine the importance of educational preference as a mediator of response.

#### Post-intervention evaluations of KT impact

##### 1) Knowledge

The screening multiple-choice test will form the baseline knowledge score. Alternate forms of this test will be devised for pediatric and musculoskeletal populations; test content will be mapped to the curriculum objectives. A bank of questions reflecting the key knowledge curriculum will be developed, and participants will be provided with alternate forms for pre- and post-test evaluations to minimize recall bias as a potential reason for score inflation.

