### Secondary objectives

1. To identify the key elements of SHIPS and e-PBL that engage participants in KT and assist them in addressing barriers to change;

2. To determine whether clinicians exhibit a decisional balance and spectrum of behaviors consistent with the Transtheoretical Model of (Readiness to) Change; and

3. To determine the relative importance of potential predictors of change, including characteristics of clinicians (years of practice, highest degree, Readiness To Change), practice settings (practice type, caseloads, years of experience), and how they affect knowledge acquisition and implementation following KT interventions.

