## Analyses

### Quantitative analyses

All data will be double-entered in SPSS 14.0. Descriptive analyses will be conducted, including checking for outliers, normality testing, and univariate correlations. The first primary analysis (Objective 1) will be a two-way repeated measures analysis of variance to determine primary unadjusted differences in absolute scores over time, and between groups for each of the three primary outcome measures: knowledge, utilization, and chart-stimulated recall scores. An analysis of covariance will be used to compare these same effects adjusting for baseline knowledge score, Readiness to Change, years of practice, and educational preference. These analyses across the e-PBL and SHIPS groups will determine the relative effectiveness of these two alternative knowledge transfer choices. Effect sizes and their 95% confidence intervals will be calculated to determine whether there are differential impacts on change in knowledge, utilization, and integration of knowledge between the two different KT approaches. For the secondary research question (Objective 2.3) on the relative importance of KT predictors, a multiple linear regression [79,80] will be used to develop models of how years of practice, educational background, caseload characteristics, educational preferences, or Readiness to Change predict changes in knowledge, utilization, or integration following knowledge transfer interventions, with KT method as a covariate.

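### Clinical area decides which knowledge test a therapist sits, but the predictor regression for knowledge change has no term for clinical area or test form

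*Protocol article*

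**What the plan says.** Under Post-intervention evaluations, 1) Knowledge, the article states: "Alternate forms of this test will be devised for pediatric and musculoskeletal populations". It adds that "test content will be mapped to the curriculum objectives" and that questions come from a bank built on the curriculum. It also says that "participants will be provided with alternate forms for pre- and post-test evaluations to minimize recall bias". So forms differ by clinical area and again between pre-test and post-test. No equating, shared items or common scale is mentioned.

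Secondary objective 3 asks about characteristics of clinicians and of "practice settings (practice type, caseloads, years of experience), and how they affect knowledge acquisition and implementation following KT interventions". Under Quantitative analyses, a multiple linear regression will model how "years of practice, educational background, caseload characteristics, educational preferences, or Readiness to Change predict changes in knowledge", utilization or integration, "with KT method as a covariate". Neither clinical area nor test form is listed, and no separate models by area are described.

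Under Group assignment procedure, minimization is carried out within orthopedic and pediatric groups at each site. Under Sample size requirements, two orthopedic tutorial groups and one pediatric group of eight are expected per intervention at each site.

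**The concern.** The regression puts change scores from different instruments on one axis. Clinical area determines the instrument, so any between-form difference in measured gain acts as an omitted variable tied to area. It passes in full to a coefficient for area itself, and in part to any predictor correlated with area, which could include degree, years of practice, Readiness to Change or caseload. Objective 3 concerns the relative importance of such predictors. A property of the tests could therefore be reported as a determinant of knowledge acquisition.

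**Working it through.** **Inputs from the article.** 3 sites × 2 interventions × 8 per tutorial group gives 48 pediatric therapists (one group each) and 96 orthopedic (two groups each), 144 in all. The total rests on 64 per group, which reproduces: a t-test at effect size 0.50, two-sided 0.05 and 80% power needs 63.8, rounded up to 64 (reading the printed Type II error of 0.80 as power). Then 2 × 64 = 128, and 128/0.9 = 142.2.

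**Assumed inputs.** The article gives no figure for a between-form artefact, so it is varied up to 0.5 SD of the change score. Orthopedic therapists are taken to sit the musculoskeletal form.

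**1. What survives in a change score.** For form f, write observed change = r_f × g + (d_post,f − d_pre,f), where g is true gain, r_f is responsiveness and d is a difficulty offset. At equal g, the pediatric minus musculoskeletal difference is

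(r_P − r_M) × g + [(d_post,P − d_pre,P) − (d_post,M − d_pre,M)].

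An offset that is constant from pre to post cancels. Unequal responsiveness does not. Nor do pre/post form differences that themselves differ by area, which is possible because the post-test uses another form.

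**2. Identification.** With columns for intercept, intervention, area and test form, the last two are identical and the design matrix has rank 3 of 4. A form term therefore cannot rescue a pediatric versus musculoskeletal coefficient. With a caseload variable that varies within area, the matrix with a form term has full rank, 4 of 4.

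**3. Area contrast with no true effect.** SE = sqrt(1/48 + 1/96) = 0.177 SD.

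| Artefact | Shift/SE | P(abs(Z) > 1.96) |
|---|---|---|
| 0.25 SD | 1.41 | 29% |
| 0.5 SD | 2.83 | 81% |

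With 128 completers (42.7 and 85.3), SE = 0.1875 and the rates are 27% and 76%. Simulating the regression on intervention and area (4,000 runs per setting) gave 20%, 40% and 79% at 0.2, 0.3 and 0.5 SD. The mean coefficient equalled the whole artefact.

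**4. A caseload feature that varies within area.** Assume a within-area SD of 1 and a gap of 0.8 between areas. With one third pediatric, area has variance 1/3 × 2/3 = 0.222. The share of the artefact that leaks is 0.8 × 0.222 / (1 + 0.64 × 0.222) = 0.178/1.142 = 0.156. At 0.5 SD that is a coefficient of about 0.08 (simulated 0.079). Simulated false-positive rates without an area term were about 6%, 9% and 16% at 0.2, 0.3 and 0.5 SD.

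**5. The same feature with area in the model.** The mean coefficient returns to about 0.00 and the false-positive rate to 4% to 5%.

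**6. Intervention contrast.** With equal arms within each area, the SHIPS versus e-PBL coefficient stayed at about 0.00 at every artefact size.

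**The case against.** The strongest objection is that caseload characteristics are never defined as pediatric versus musculoskeletal. The article calls that split a clinical area or area of practice, and elsewhere uses practice type for PT/OT and practice area for urban/rural. If caseload means volume or case mix, it varies within each form and can be separated from it. This stands. A reader might infer that no caseload effect on knowledge can be disentangled from the test; the article does not support that, and the 29% to 81% range applies only to the area contrast.

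Second, a constant difficulty gap cancels in change scores. This also stands, but only for a gap that is the same at pre-test and post-test.

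Third, the forms share one curriculum and question bank, and equating or a fuller covariate list may sit in a document not shown. Pooling without an area term is inferred from a model description that names its predictors and one covariate, not from an explicit statement. That limits certainty. Shared curriculum content, however, does not make the forms equally difficult or responsive, and the regression as described lacks the term.

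Fourth, the artefact sizes and the 0.8 SD gap are assumptions. They are, and the results are given as ranges for that reason.

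**Conclusion.** The concern holds in limited form. Followed as written, the knowledge-change regression lets between-form differences in responsiveness, or in pre/post difficulty, bias predictors whose mix differs by clinical area. If area is one of the caseload characteristics, its effect on knowledge is not identifiable. The false-positive rate for that contrast is about 29% to 81% under an assumed 0.25 to 0.5 SD artefact. For features that vary within area it is about 6% to 16% under 0.2 to 0.5 SD and an assumed 0.8 SD gap.

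The reach is one outcome within one secondary objective. A reader might infer that the comparison of SHIPS with e-PBL is also biased. It is not, because allocation is balanced within orthopedic and pediatric groups. Utilization and chart-stimulated recall do not use this test and are not affected by it.

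**What to change.** In the knowledge-change regressions, add clinical area (orthopedic/pediatric, the stratum already used for allocation) as a fixed term, and interpret the other predictors as within-area effects. Name it so that it is not confused with the urban/rural variable. State that the area coefficient for knowledge will not be reported as a caseload or setting effect unless the forms are shown to be equated. Area effects may still be reported for utilization and chart-stimulated recall.

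Standardizing scores by the baseline mean and SD of each form is not an adequate substitute. The post-test uses a different form, and the 75% exclusion rule truncates the baseline distribution.

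The change is to analysis wording only, with no new data and no change to sample size. Its price is the pediatric versus musculoskeletal comparison on knowledge, which unlinked forms cannot support.

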##### 2) Utilization

Chart audit will be used to measure utilization of outcome measures. In many situations, chart audit does not accurately represent the content of a clinical interaction because not all information is recorded [74]. However, in our case the reverse is true. Specific self-report forms are required to administer outcome measures and will provide direct evidence of utilization. Charts will be selected for a chart audit procedure as follows: a) one day from each participant's previous month of practice will be selected randomly, b) a list of patients seen on that day will be generated, and c) five patient charts will be selected randomly from that daily list. Using a standardized data extraction form, the entire chart record will be audited to determine the total numbers of outcome measures used, the frequency of use, the timing of use (i.e., every session, at evaluation and discharge), and the specific outcome measures used. In addition, it will be recorded whether scales were scored correctly, and whether the scales were specifically mentioned in goal setting or discharge planning.

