**Method/Design:**

Physical and occupational therapists (n = 144) will be recruited in partnership with the national professional associations to evaluate two different KT interventions with the same curriculum: 1) Stakeholder-Hosted Interactive Problem-Based Seminar (SHIPS), and 2) Online Problem-Based course (e-PBL). SHIPS will consist of face-to-face problem-based learning (PBL) for 2 1/2 days with outcome measure developers as facilitators, using six problems generated in consultation with participants. The e-PBL will consist of a 6-week web-based course with six generic problems developed by content experts. SHIPS will be conducted in three urban centers in Canada. Participants will be block-allocated by a minimization procedure to either of the two interventions to minimize any prognostic differences. Trained evaluators at each site will conduct chart audits and chart-stimulated recall. Trained interviewers will conduct semi-structured interviews focused on identifying critical elements in KT and implementing practice changes. Interviews will be transcribed verbatim. Baseline predictors including demographics, knowledge, attitudes/barriers regarding outcome measures, and Readiness to Change will be assessed by self-report. Immediately post-intervention and 6 months later, these will be re-administered. Primary qualitative and quantitative evaluations will be conducted 6-months post-intervention to assess the relative effectiveness of KT interventions and to identify elements that contribute to changing clinical behavior. Chart audits will determine the utilization of outcome measures (counts). Incorporation of outcome measures into clinical reasoning will be assessed using an innovative technique: chart-stimulated recall.

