## Background

Patient-oriented health outcomes are key to assessing health care in chronic illness. Chronic disability, as a result of adult musculoskeletal or childhood disorders, is profound and comprises a large component of practice for a variety of health care providers. Musculoskeletal diseases of adulthood are the leading cause of long-term disability in Canada, accounting for roughly one-third of the country's long-term disability costs [1]. Childhood disorders also account for a large percentage of disability treatment costs with 1 in 12 children now considered disabled; increasing rates are attributable to improvements in medical care that save more compromised children, broader definitions of disability, and a greater willingness to report handicaps [2]. Due to the chronic nature of these disorders, treatment is focused on minimizing disability and improving quality of life. Standardized measurement of the impact of interventions on these health outcomes is fundamental to advancing clinical practice and research.

The current use of patient-oriented outcome measures in research and practice is deficient, despite the fact that health care professionals recognize the importance of measuring health outcomes and efforts have been made to transfer available knowledge into practice. These efforts include national initiatives by the professional associations of both occupational therapists (OT) and physical therapists (PT), traditional workshops [3], published editorials [4], scientific articles [5-16], textbooks [17], professional association endorsements, and promotion of an outcomes database. While agreement with the need for outcome measures is consistently high, utilization remains low across professional groups dealing with these chronic problems, such as Rehabilitation [18], Rheumatology [7,19], and Orthopaedic Surgery [20]. Rehabilitation is commonly performed by PTs and OTs in a variety of practice settings. As few knowledge transfer studies have included these providers, we decided to focus on PTs and OTs for this study. The needs have been well established in this area, and the investigators have established partnerships with the associated national professional associations who will facilitate the current project and arising national KT initiatives.

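### The 6-month utilization count covers each patient's whole chart with no cut at the intervention date, so entries made before the teaching dilute the comparison of SHIPS with e-PBL

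*Protocol article*

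**What the plan says.** Chart audit measures utilization. The article's section 2) Utilization sets out the sampling: "one day from each participant's previous month of practice will be selected randomly", the patients seen that day are listed, and "five patient charts will be selected randomly from that daily list". These steps choose patients; they do not restrict which entries in a chart are counted. For the chosen charts, "the entire chart record will be audited to determine the total numbers of outcome measures used". The same form also takes "the frequency of use, the timing of use (i.e., every session, at evaluation and discharge), and the specific outcome measures used".

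The abstract describes utilization as counts and fixes the timing: "Primary qualitative and quantitative evaluations will be conducted 6-months post-intervention". Quantitative analyses lists utilization as one of three primary outcomes, to be analysed by a "two-way repeated measures analysis of variance to determine primary unadjusted differences in absolute scores over time" and between groups. An analysis of covariance follows, adjusting for baseline knowledge, Readiness to Change, years of practice and educational preference. Sample size requirements sets the study to detect an effect of 0.50 on any of the three outcomes, utilization included.

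**The concern.** The patients audited were seen in the month before the audit, but some may have been under care for much longer. The Background gives a reason to expect this: "Due to the chronic nature of these disorders, treatment is focused on minimizing disability and improving quality of life". Sampling from one day's list also favours patients who attend often or over a long period.

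If such a chart was opened before the intervention, its early entries record what the therapist did before being taught. Neither arm can change them. They add a similar amount to both arms' totals together with extra variation, so the difference shrinks relative to the level and spread of the count. A real difference in practice could then be missed on an outcome that the study claims to be powered for. Subtracting a baseline value in the repeated measures analysis would not remove the old entries from the 6-month total.

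**Working it through.** **1. The protocol's own figure.** Inputs from Sample size requirements: two-sided alpha 0.05, effect size d = 0.50, and a value of 0.80 that the article labels Type II error. A two-sample t-test with power 0.80 needs 63.8, so 64 per group and 128 in all. Allowing for dropout, 128/0.9 = 142.2, given as 142 and rounded up to 144. The figure reproduces with 0.80 read as power; a literal Type II error of 0.80 would need only about 11 per group.

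**2. Dilution on the protocol's scale.** Let f be the share of all counted entries that predate the intervention, equal in both arms. Hold the total count and its standard deviation fixed. Only the share 1 − f can respond, so the standardized effect is d × (1 − f) = 0.50 × (1 − f). The article gives no value for f, so a range is shown.

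| f (assumed) | effect size | power at 64 per group | n per group for 80% power |
|---|---|---|---|
| 0 | 0.50 | 0.80 | 64 |
| 0.10 | 0.45 | 0.71 | 79 |
| 0.20 | 0.40 | 0.61 | 100 |
| 0.30 | 0.35 | 0.50 | 130 |
| 0.40 | 0.30 | 0.39 | 176 |
| 0.50 | 0.25 | 0.29 | 253 |

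**3. What chart length gives such an f.** For an audit 6 months after the intervention and entries spread evenly over a chart of L months, f = (L − 6)/L when L exceeds 6, and 0 otherwise. This gives 0 for 6 months or less, 3/9 = 0.33 for 9 months, 6/12 = 0.50 for 12 months and 18/24 = 0.75 for 24 months. The f in the table is an average over all audited entries. For example, if 60% of entries come from 12-month charts and the rest from charts opened after the intervention, f = 0.60 × 0.50 = 0.30.

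**4. What a date cut recovers.** Removing the old entries leaves the expected difference in counts unchanged and lowers the standard deviation. If the standard deviation falls in proportion to the count, the effect returns to 0.50. If all variation were Poisson, it would fall only by √(1 − f), and the effect would be 0.50 × (1 − f)/√(1 − f) = 0.50 × √(1 − f). At f = 0.30 that is 0.42, against 0.35 without the cut.

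**5. Is the normal-theory test at fault?** In a simulation (64 per group, five charts per therapist, gamma-Poisson counts, an assumed mean of 8 visits per chart and 0.15 measures per visit), the t-test on skewed counts held its type I error at about 0.04 to 0.06. Uneven visit numbers did cost power. At a rate ratio of 1.5 and the lowest of three assumed dispersions, power was about 0.80 for a per-visit rate and 0.67 to 0.73 for raw counts. That is lost efficiency, separate from the dilution in step 2.

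**The case against.** The best reply is that the size is unknown. No chart length is given. The Background speaks of chronic disorders, which is not the same as long treatment episodes, and two of the three tutorial groups per intervention and site are expected to be orthopedic. Many charts may have been opened after the intervention and carry no old entries. Reading the whole chart also has a purpose, since measures may be used at first evaluation and at discharge. All of this stands. It limits the size of the problem, not its direction, and reading the whole chart does not require counting all of it.

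It may also be said that a journal article condenses. Here, however, the article states which part of the chart is counted.

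A reader might infer four stronger points, which the document does not support:

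- That analysis of variance on counts itself dilutes the effect, or that a negative binomial model is needed. Type I error stays near 5%, the article plans normality and outlier checks, and the choice of a count model is commonly left to an analysis plan.
- That visits are ignored altogether. The named analyses do not adjust for them, but frequency and timing of use are extracted and could support a per-visit measure. A log-visits offset is not clearly right either, because use at evaluation and discharge does not grow with visits.
- That differing visit numbers make the result uninterpretable across practice types. Group assignment procedure minimizes within orthopedic and pediatric groups at each site, so practice type is balanced between arms.
- That a true rate ratio of 2.0 must shrink to 1.50, 1.33 or 1.25 with 6, 12 or 18 prior months, from (prior + 6 × 2)/(prior + 6). This holds one arm at its old rate. Both arms are active. If the comparator also doubles its use, the ratio is (prior + 6 × 4)/(prior + 6 × 2), which gives 30/18 = 1.67, 36/24 = 1.50 and 42/30 = 1.40.

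**Conclusion.** The point holds as a matter of outcome definition. As written, the 6-month utilization count includes pre-intervention entries from any chart opened before the intervention, and this biases the standardized or relative difference between the arms toward zero on a primary outcome. Power falls from 0.80 to about 0.71, 0.50 or 0.29 at pre-intervention shares of 10%, 30% or 50%. This assumes an equal share in both arms, an unchanged standard deviation and 64 analysed per group. At a share of zero there is no loss, and the document cannot say where in the range the study would fall. The case for changing the definition rests on its certain direction and low cost, not on any one of these figures.

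**What to change.** Define the primary utilization outcome as the number of outcome measures in chart entries dated after the end of the participant's intervention and up to the audit. Use the same window length in both arms: SHIPS lasts 2 1/2 days and e-PBL six weeks, so the window should start from each participant's own end date. Record the date of each entry and the number of visits in the window. Keep earlier entries only as pre-intervention information, outside the outcome.

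Use per visit, or adjustment for visits, can be an optional sensitivity analysis. The planned analysis of variance and covariance can stay.

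The cost is a date field and a visit count on an extraction form already in use, settled before the first audit so that charts need not be opened again. The downside is fewer countable events per chart, and for long-standing patients the first evaluation will fall outside the window.
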